## Abstract

**Background:**

Procedural sedation is a core skill of the emergency physician. Bolus administration of propofol is widely utilised in UK emergency departments to provide procedural sedation. Bolus administration of propofol, titrated to an endpoint of sedation, has a rapid effect but can easily result in apnoea and loss of airway patency. The use of a target-controlled infusion of propofol allows for controlled titration to an effect site concentration and may reduce the rate of adverse incidents. Target-controlled infusion of propofol is not currently used in emergency departments.

The primary aim of this feasibility study is to ensure that propofol target-controlled infusion (TCI) is acceptable to the patient and that recruitment rates are adequate to power a randomised controlled trial comparing propofol target-controlled infusion versus bolus administration.

**Methods:**

This study will recruit in four emergency departments in Scotland, UK. Patients aged 18–65 years with anterior shoulder dislocation, weighing ≥ 50 kg and fasted ≥ 90 min, will be screened. Recruited patients will undergo emergency reduction of a dislocated shoulder facilitated by procedural sedation utilising TCI of propofol.

The widespread adoption of TCI propofol by emergency departments will require evidence that it is safe, potentially effective, patient centred and a timely method of providing procedural sedation. The primary endpoint will be acceptability measured by patient satisfaction. The secondary endpoints will include incidence and severity of adverse events, number of shoulder reduction attempts, nursing opinion of patient experience, patient’s reported pain score and time from commencement of TCI propofol sedation to desired sedation level.

The study will be open for recruitment from April 2017 to December 2018.

**Discussion:**

If the study demonstrates patient acceptability with adequate recruitment, we will be in a position to determine the feasibility of progression to a randomised controlled clinical trial of TCI compared to bolus administration of propofol.

**Trial registration:**

ClinicalTrials.gov Identifier: NCT03442803. Registered retrospectively on 22 February 2018.

**Electronic supplementary material:**

The online version of this article (10.1186/s40814-019-0412-y) contains supplementary material, which is available to authorized users.

## Background

### Sedation in the emergency department

Procedural sedation and analgesia (PSA) has long been a core skill of the emergency physician, although over the last decade, developments in patient monitoring and the use of newer sedative and analgesic agents have served to improve both safety and efficacy [1]. Despite these advances and their consolidation into well-designed guidelines [2, 3], concern regarding the safety of emergency department (ED) PSA persists [4, 5].

More specifically, concerns have been raised regarding the use of propofol, an ultra-short acting anaesthetic agent [6]. The practice of using sub-anaesthetic doses of propofol to achieve sedation in ED PSA originated around the turn of the millennium [7] and has since become the most common choice of sedative in the ED [4, 8]. Propofol offers a number of advantages as a sedative agent, including a short onset and recovery time, amnesiac properties and good efficacy [9–11]. The cost of these properties is, in part, a narrow therapeutic range. Propofol in the ED is currently given as a repeated bolus (normally a few millilitres at a time until the desired effect is achieved).

When given as a bolus, propofol will induce a spectrum of states up to and including general anaesthesia, dependent on the dosage. The correlation between dose and effect varies based on several patient factors. Whilst targeting a state of sedation, it is possible for the operator to ‘overshoot’ moving rapidly from conscious sedation to deep sedation to general anaesthesia. The inadvertent induction of general anaesthesia may result in unanticipated complication. The principle complications associated with accidental over-sedation or general anaesthesia relate to the patency of the patient’s airway. The reported frequency of airway complications during ED PSA with propofol range from 5.0 to 9.4% [7]; this includes a rate of supplemental ventilation of between 3.0 and 9.4%, with oxygen desaturation occurring in between 5 and 7% of cases [12]. In addition, the bolus administration of propofol may result in transient hypotension [12]. Despite being a relatively short-lived effect, this may be pronounced in those with intravascular volume depletion [13] or in the elderly [14], and in some may be profound, with one series demonstrating that 3.5% of those undergoing PSA with propofol experience ≥ 20% falls in blood pressure [15]. At first inspection, the reported rate of complication may appear low and has by some been interpreted as evidence of the relative safety of ED PSA; however, alternative views have been expressed in the context of much lower rates of adverse events seen in elective painful procedures requiring conscious sedation [6, 16]. This is compounded by the non-standard way in which adverse events have been reported across studies [17].

A potential solution to the adverse events experienced with the bolus administration of propofol is the use of a target-controlled infusion (TCI). This method is widely used in anaesthetic practice, and whilst the PK remains the same irrespective of if you give a bolus or infusion of propofol, TCI allows the titration in perhaps a more controlled manner.

### Target-controlled infusion

The aim when administering propofol, as with any drug, is to induce a desired clinical effect, in this context a level of sedation. As previously alluded to, when administering propofol in a bolus fashion or as a fixed rate infusion, without regard to those factors which cause biologic variability (e.g. age, gender, weight), it is difficult to accurately and consistently predict clinical effect. The development, in the early 1990s, of computer-assisted infusion devices, for the first time, allowed the clinician to target a plasma concentration, with the pump automatically altering the rate of infusion based on a pre-programmed pharmacokinetic model [18]. These target-controlled infusion (TCI) devices have undergone significant development and are now in widespread clinical use. Their operation uses a mathematical mode that reflects a theoretical ‘three-compartment’ model that may comprise the central compartment (plasma), and two peripheral compartments (highly perfused tissue, e.g. brain, and poorly perfused tissue, e.g. adipose). In a state of equilibrium, propofol will diffuse between compartments at a constant rate. These rate constants have been used in pharmacokinetic models to mathematically predict the plasma concentration and latterly the effect site concentration, in this case that in the brain [19].

In practical terms, TCI allows the operator to more accurately target a specific clinical effect. When propofol is administered as a bolus, the operator is likely to either underdose, delivering an insufficient effect site concentration, or overdose, exceeding the desired effect site concentration. TCI allows the operator to titrate to effect and then to maintain a steady state, potentially eliminating the risk of ‘over shooting’ and reducing the rate of adverse events. TCI is not without limitation. PK models are an estimate as they have been derived from a healthy population, but any inherent inaccuracy is consistent in different populations and accounted for by careful titration.

The use of propofol TCI has been studied in a number of settings, including gastrointestinal endoscopy [20–22], dental surgery [23, 24], oocyte retrieval [6] and bronchoscopy [25, 26]. To our knowledge, propofol TCI in sedation has not been studied in an ED setting. Trials have demonstrated a good safety profile for propofol TCI, with at least one large randomised controlled trial [20] in an endoscopy setting, showing a reduction in both respiratory and cardiovascular adverse events in comparison to the bolus administration of propofol. Unfortunately, trials to date have suffered from a high degree of heterogeneity, leading the Cochrane review, on the subject of propofol TCI versus manually controlled infusion in both general anaesthesia and sedation, to conclude that there was insufficient evidence to make firm recommendations regarding its use in clinical practice [27].

### Study rationale

There exists continued controversy over the use of propofol in ED PSA; this is despite its widespread existence in clinical practice for at least a decade. These concerns are not limited to the ED setting and are primarily related to the pharmacological properties of the drug itself and its potential for harm. The bolus administration of propofol, aimed at a target of sedation, offers several advantages over more traditional agents, yet these advantages are also its limitations. The use of a target-controlled infusion makes titration of propofol easier with fewer adjustments, thus potentially reducing the incidence of adverse incidents.

The incidence of adverse events using bolus propofol versus TCI propofol in the emergency department will be recorded in the future randomised controlled trial (RCT). This current feasibility study is needed first before a main trial in order to provide evidence that TCI is safe, potentially effective, patient centred and a timely method of providing procedural sedation. It will also provide information about recruitment to ensure that the randomised controlled trial can be adequately powered.

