### Progression

Progression to a multi-centre randomised control trial will require evidence of the ability to adequately recruit and that it is safe, potentially effective, patient centred and a timely method of providing procedural sedation.

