### Sample size rationale

A formal sample size should not be calculated for this feasibility study [30]. We aim to recruit at least 20 patients within a fixed time period to allow calculation of recruitment rate. This time period was agreed by reviewing the average number of anterior shoulder dislocations attending at each site per week.

Recruitment commenced on April 2017 and will continue until 31 December 2018. If 13 patients per week present for 86 weeks of the planned duration of the study, then a total of 1118 potential patients could potentially be recruited. After we account for those patients who are willing and able to give consent (approximately 1 in 5) to research in an emergency care setting (1118/5), we estimate that 224 potential patients could be recruited. A total of one in five of the consultant staff at the recruiting sites was trained to undertake this procedure using TCI propofol (224/5) leaving 45 patients presenting at any time during a 24-h period. The consultant presence in the emergency department is approximately 12 h per 24 h (45/2), leaving approximately 22 patients from the total of 1116 anterior shoulder dislocations.

This information will allow assessment of the feasibility of recruiting to an adequately powered randomised controlled trial with the incidence of adverse events as the primary endpoint.

Emergency departments have a unique set of challenges that make recruiting to research studies difficult [31]. Patients may present at any point, 24 h per day, 7 days a week to an unpredictable, high-risk setting. All research activity is undertaken by emergency medicine consultants.

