### Planned analysis

The plan of analysis for study data will be designed with the assistance of a biomedical statistician from the University of Strathclyde. Descriptive statistics will be presented.

Following the completion of this feasibility study, we plan to proceed to an RCT. The primary endpoint for our multi-centre RCT will be the incidence and severity of adverse events.

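### About 20 patients on TCI cannot supply the evidence of safety that the protocol names as a purpose and as a condition for progression

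*Protocol article*

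**What the plan says.** The Study rationale gives the reason for doing this study before a main trial: it is to "provide evidence that TCI is safe, potentially effective, patient centred and a timely method of providing procedural sedation". The softening adverb in that phrase applies to effectiveness, not to safety. The Progression section repeats the point as a requirement. Going on to a multi-centre randomised trial "will require evidence of the ability to adequately recruit and that it is safe", with no numerical criterion.

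The Sample size rationale ties the number of patients to recruitment, not to safety: "We aim to recruit at least 20 patients within a fixed time period to allow calculation of recruitment rate". Its forecast ends by "leaving approximately 22 patients from the total of 1116 anterior shoulder dislocations". All recruited patients receive TCI. Adverse events are a secondary endpoint, and of the analysis the article says "Descriptive statistics will be presented".

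The Background section on sedation in the emergency department gives the safety figures that motivate the work: "The reported frequency of airway complications during ED PSA with propofol range from 5.0 to 9.4" per cent. The Study rationale, Planned analysis and Discussion leave adverse events under TCI versus bolus to the future randomised trial. For progression, the Discussion asks only that TCI offer the potential for better safety.

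**The concern.** Two sections treat safety as something this study can establish, and one of them makes it a gate to the next trial. A gate needs a result that can open it on the evidence. Here the best possible result, no adverse event in any patient, is compatible with event rates well above those that prompted the research.

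What is at stake is the inference drawn at the progression decision. With no threshold stated, an uneventful small series could be taken as meeting the condition, although such a series is quite possible when TCI is no safer than the quoted figures. The sections also pull against each other. If the randomised trial is to establish comparative safety, evidence that TCI is safe should not be a precondition for starting it.

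**Working it through.** **Inputs.** From the Sample size rationale: 13 presentations a week, 86 weeks, factors of 1/5 (consent), 1/5 (trained consultants) and 1/2 (consultant hours), and a target of at least 20. From the Background: airway complications in 5.0 to 9.4%. The 95% confidence level is an assumption, since the article states none; one- and two-sided limits are both shown.

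**The plan's own figure.** 13 × 86 = 1118; 1118 / 5 = 223.6; 223.6 / 5 = 44.7; 44.7 / 2 = 22.4. The stated forecast of about 22 is reproduced. (The section gives the total once as 1118 and once as 1116. The product is 1118, and the difference does not affect this point.)

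**Upper limit with zero events.** The exact (Clopper-Pearson) limit is 1 − α^(1/n), with α = 0.025 two-sided and 0.05 one-sided.

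| n | Two-sided 95% | One-sided 95% |
|---|---|---|
| 20 | 1 − 0.025^(1/20) = 16.8% | 1 − 0.05^(1/20) = 13.9% |
| 22 | 1 − 0.025^(1/22) = 15.4% | 1 − 0.05^(1/22) = 12.7% |

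All four limits exceed 9.4%, so the result does not depend on sidedness. With a single event in 20, the two-sided interval runs from 0.1% to 24.9%.

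**Chance of an uneventful series if the true rate lies in the quoted range.** P(0 events) = (1 − p)^n.

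| n | p = 5.0% | p = 9.4% |
|---|---|---|
| 20 | 0.950^20 = 35.8% | 0.906^20 = 13.9% |
| 22 | 0.950^22 = 32.4% | 0.906^22 = 11.4% |

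The expected number of events in 20 patients is 20 × 0.050 = 1.0 to 20 × 0.094 = 1.9.

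**Event-free patients needed for the upper limit to fall below a quoted rate.** n = ln(α) / ln(1 − p), rounded up.

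- For 9.4%: ln(0.025) / ln(0.906) = 37.4, so 38 (two-sided); 31 one-sided.
- For 5.0%: 72 (two-sided); 59 one-sided.

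Even the most lenient of these, 31, exceeds the forecast of 22. These counts show the scale of the gap. They are not a proposed sample size.

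**The case against.** The strongest reply is that the protocol never undertakes to rule out 5.0 to 9.4%. Those figures are background. They cover airway complications only, whereas the endpoint uses the World SIVA tool, which may count a wider set of events. The Background itself warns that adverse events have been reported inconsistently across studies. The patients here are also selected: ASA I or II, aged 18 to 65, at least 50 kg and fasted. The primary aim is acceptability and recruitment, safety is a secondary objective defined as the incidence of adverse events, and the comparison with bolus is reserved for the randomised trial. All of this stands, and it limits the point to the wording of two sections.

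It also rules out several stronger readings that a reader might infer:

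- That the study is too small. The number was chosen to estimate recruitment, and a formal calculation is expressly disclaimed, which is acceptable for a feasibility study.
- That the study fails because it cannot separate TCI from bolus. The documents do not ask it to.
- That the abstract needs the same correction. Its safety sentence concerns what widespread adoption would require, and it is sound.
- That the description of the analysis is at fault. Descriptive statistics do not exclude intervals, and such detail commonly belongs in an analysis plan, which is not shown.
- That an uneventful series is to be expected if TCI is no safer. At 5.0% it is fairly likely (36%), but at 9.4% it is not (14%).
- That the investigators would report a clean series as proof of safety. Nothing in the text shows this.

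What the reply does not remove is the stated progression condition. It is firmer than the Discussion's version, and no method of analysis changes what zero events in 20 patients can exclude.

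**Conclusion.** The point holds as one about claim and criterion, not about design. The Study rationale and Progression sections attribute to the study a property that 20 to 22 patients cannot give it: the most favourable outcome excludes only rates above about 17% (20 patients) or 15% (22 patients). This rests on an exact two-sided 95% limit and on the protocol's own recruitment forecast; one-sided limits lead to the same conclusion. The 5.0 to 9.4% range serves only as a yardstick of scale, and its match to the study's endpoint and population is loose. The Progression section also needs reconciling with the Discussion, which states a weaker safety condition, and with the sections that leave the safety comparison to the randomised trial.

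**What to change.** In the Study rationale and Progression sections only:

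- Replace the promise of evidence of safety with a preliminary description of adverse events.
- Say there that zero events in about 20 patients would exclude only rates above about 17%.
- Make safety a progression criterion that can raise a concern about going on, not one that an uneventful series can pass, and bring the Progression and Discussion sections into agreement.
- Give the adverse event proportion used for the progression decision with its exact 95% confidence interval.

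The abstract can stay as it is. The cost is a more modest stated claim and one interval; sample size and conduct of the study do not change.

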### Aim

The primary aim of this feasibility study is to ensure that propofol TCI is acceptable to the patient and that recruitment rates are adequate to power a future RCT.

Secondary objectives are:Safety:◦ Incidence of adverse eventsPotential effectiveness:◦ Successful completion of the procedure◦ Number of reduction attemptsPatient centred:◦ Patient-reported pain scores◦ Nursing opinion of the patient’s experience◦ Patient recall of the procedure◦ Free text comments from all staff at the end of the procedureTimely:◦ Time taken to reach the appropriate sedation level◦ Time from commencement of sedation to ‘fit for discharge’

### Progression

Progression to a multi-centre randomised control trial will require evidence of the ability to adequately recruit and that it is safe, potentially effective, patient centred and a timely method of providing procedural sedation.

## Methods

### Study design

Multi-centre feasibility study

### Study population

Adult patients (≥ 18 years), requiring sedation to facilitate the reduction of an acute traumatic anterior shoulder dislocation in the emergency department

### Inclusion criteria

Aged 18–65 yearsClinical and/or radiological evidence of acute anterior shoulder dislocationAmerican Society of Anesthesiologists (ASA) Physical Status Classification I or IIFasted ≥ 90 min [2, 3, 28, 29]Weight ≥ 50 kg

### Exclusion criteria

Inability to provide or refusal of informed consentPrevious attempt at reduction during the same presentationPreviously enrolled in the studyClinical and/or radiological evidence of acute posterior shoulder dislocationClinical and/or radiological evidence of concomitant ipsilateral upper limb fracture (with the exception of an isolated avulsion fracture of the greater tuberosity or a fracture of the glenoid labrum)Concomitant multi-system injuryHistory of difficult intubation/airway surgeryASA grades III, IV or VHaemodynamic instabilityPregnancyContraindication to sedationAllergy to study drugs or eggsClinician decisionMorphine administration within the preceding 20 min prior to starting TCI (can be included if > 20 min)

There is no objection to subsequent co-enrolment of patients to clinical trials amongst those already enrolled to ProTEDS.

### Sample size rationale

A formal sample size should not be calculated for this feasibility study [30]. We aim to recruit at least 20 patients within a fixed time period to allow calculation of recruitment rate. This time period was agreed by reviewing the average number of anterior shoulder dislocations attending at each site per week.

Recruitment commenced on April 2017 and will continue until 31 December 2018. If 13 patients per week present for 86 weeks of the planned duration of the study, then a total of 1118 potential patients could potentially be recruited. After we account for those patients who are willing and able to give consent (approximately 1 in 5) to research in an emergency care setting (1118/5), we estimate that 224 potential patients could be recruited. A total of one in five of the consultant staff at the recruiting sites was trained to undertake this procedure using TCI propofol (224/5) leaving 45 patients presenting at any time during a 24-h period. The consultant presence in the emergency department is approximately 12 h per 24 h (45/2), leaving approximately 22 patients from the total of 1116 anterior shoulder dislocations.

This information will allow assessment of the feasibility of recruiting to an adequately powered randomised controlled trial with the incidence of adverse events as the primary endpoint.

Emergency departments have a unique set of challenges that make recruiting to research studies difficult [31]. Patients may present at any point, 24 h per day, 7 days a week to an unpredictable, high-risk setting. All research activity is undertaken by emergency medicine consultants.

### Primary endpoints

Patient satisfaction—visual analogue scale (VAS) (Additional file 1) [32]Percentage of patients recruited vs percentage of patients approached

### Secondary endpoints

Incidence and severity of adverse events per World Society for Intravenous Anaesthesia (SIVA) adverse event sedation reporting tool [33]The successful reduction of the anterior shoulder dislocationNumber of reduction attemptsPatient-reported pain score VAS (Additional file 2) [32, 34]Nurse opinion of patient experience VAS (Additional file 3) [32]Patient recall of the procedure [35]Free text comments from all staff at the end of the procedureTime from commencement of induction to Modified Observer’s Assessment of Alertness/Sedation Scale (OAA/S) 3 [36]Time from commencement of sedation to fit for discharge [2]◦ Patient returned to their baseline level of consciousness◦ Vital signs are within normal limits for that patient◦ Respiratory status is not compromised◦ Pain and discomfort have been addressed

Figure 1 displays the Standard Protocol Items: Recommendations for Interventional Trials (SPIRIT) figure of enrolment, interventions and assessments.

